### Interventions

Participants in the control arm used the devices but received no other interventions and were not asked to conduct goal setting. Participants randomized to 1 of the 3 gamification arms conducted goal setting during the in-person visit. This included selecting a HbA_1c_ reduction goal (1.5%, 2%, or 2.5%), a weight loss goal (6%, 7%, or 8% of their baseline weight), or an increase in daily step counts (33%, 40%, or 50% greater than baseline, or any step goal that is at least 1500 steps above their baseline). A number of design considerations were incorporated to help participants achieve their goals while minimizing risks. First, the weight loss goal was set for a gradual decline over the first 26 weeks and then to maintain that level during the next 26 weeks. Participants were given a weight target each week, and if not achieved, the target remained the same for the following week. Second, participants had a 4-week ramp up toward their daily step goal. For example, a participant with a baseline of 6000 steps per day and goal of 8000 steps per day was asked to achieve goals of 6500, 7000, 7500, and 8000 for each of the first 4 weeks of the study. Then, they were asked to maintain the 8000 steps per day goal for the remainder of the study. Finally, the HbA_1c_ goal was set for the 6-month time point and was expected to be maintained through 1 year.

Participants in the gamification arms were entered into an intervention approach based on prior work that used points and levels designed to incorporate insights from behavioral economics [19,20]. First, participants were asked to sign a precommitment pledge to strive to achieve their goals during the study. Precommitment has been demonstrated to motivate behavior change [32,33]. Second, at the beginning of each week, the participant received 70 points (10 for each day that week). If the participant did not weigh-in, they lost 10 points from their balance. This leverages loss aversion, which has demonstrated that loss framing is more effective at motivating behavior change than gain framing [14-16]. Third, at the end of each week, if participants had at least 40 points, achieved their weekly weight target, and averaged at or above their daily step goal, they were moved up a level (levels from lowest to highest: blue, bronze, silver, gold, and platinum). If not, participants were dropped a level. This design creates achievable goal gradients—the notion that the next highest level was attainable—and a sense of social status and progression through the game. All participants begin at the silver level, so that they will feel the loss of dropping to bronze if they do not achieve enough points in the first week. Participants who finished in the platinum level received a trophy, and participants who finished in the gold level received a medal. Fourth, participants got a new set of 70 points every Monday. This design leverages the *fresh start effect* that is the tendency for aspirational behavior around temporal landmarks such as the beginning of the year, month, or week [34]. Fifth, to help re-engage participants who are struggling to meet their goals at months 3, 6, and 9 (defined as being in the blue or bronze levels of the game), the study coordinators called them to inquire about their progress in the study, reset them to the silver level, and offered them the opportunity to readjust their goals based on their initial options. Sixth, the participants’ primary care physician was mailed a monthly report with data on their change in weight, step goals, HbA_1c_, and LDL-C (Figure 2). A copy of this letter was also mailed to the participant. Finally, the game varied based on the social incentive arm described as follows:

In the supportive social incentive arm, participants were asked to identify a family member or friend to be their support sponsor. This sponsor is encouraged to support the participant in their progress during the study. A weekly report is sent by email to the sponsors with the participants’ performance including their points and level (Figure 3).In the competitive social incentive arm, participants are placed into a group of 3 participants. These participants typically did not know each other before the study but were introduced to each other by email at the beginning of the intervention. At the end of each week, the participants receive an email with a leaderboard that ranks them on their cumulative points in the study thus far and also displays their level. In the event of a tie in total cumulative points, the participants will be secondarily ranked on level. This feedback may help to induce participants to compete for the top spot among the group.In the collaborative social incentive arm, participants are placed into a group of 3 participants as a team. These participants typically did not know each other before the study but were introduced to each other by email at the beginning of the intervention. Each day, one of the members of the group is randomly selected to represent his or her team for that day, and that information is shared with the entire group. If the participant selected weighed in on the previous day, the team keeps their points. If he or she did not, then the team is told that they lost 10 points. In this design, each person is accountable to the others in the team, and this may induce a collaborative effort to meet their daily goals. The entire team moves up a level only if the team has at least 40 points by the end of the week.

**Figure 2 figure2:**
[figure not shown]
Example of a physician letter.

**Figure 3 figure3:**
[figure not shown]
Example of support partner messages.

### Outcome Measures

The primary outcomes were change in HbA_1c_, change in weight in pounds, and change in mean daily steps from baseline to the end of the 1-year study. Secondary outcomes include the change in LDL-C levels from baseline to end of the 1-year study, and change in mean daily steps, weight in pounds, and HbA_1c_ from baseline to the 6-month time point of the study.

### Power

We estimated that a sample size of 360 participants (90 per arm) will provide at least 80% power using a conservative Bonferroni adjustment of the type I error rate with a 2-sided alpha of .017 and accounting for a dropout rate of 10% to detect (1) an 1100-step change in physical activity with a standard deviation of 2000 steps; (2) a 6-lb change in weight with a standard deviation of 10 lbs; and (3) a 0.8% change in HbA_1c_ with a standard deviation of 1.5%. These values are based on prior work [19,20,35,36]. This trial has been powered for 2 phases of hypothesis testing. In the first phase, we will compare each of the 3 intervention arms with control. In the second phase, we will compare successful intervention arms with each other. We expect that the magnitude of difference between intervention arms will be less than that of successful intervention arms compared with control. For this second phase of analyses, we will use a conservative Bonferroni adjustment of the type I error rate with a 2-sided alpha of .017 to adjust for up to 3 comparisons. As only intervention arms that demonstrated a significant difference with the control are compared with each other in the second phase, the overall family-wise error rate of this 2-phase procedure is controlled at 0.05 [37].

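### The claim of power for both testing phases rests on one calculation, which covers comparisons between intervention arms only if those differences are nearly as large as the listed effects

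*Protocol article*

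**What the plan says.** All the relevant text is in the Power section of the protocol article. It gives one calculation: 360 participants, 90 per arm, two-sided alpha of .017 and 10% dropout. This "will provide at least 80% power" for one effect per outcome: "an 1100-step change in physical activity with a standard deviation of 2000 steps", 6 lb with a standard deviation of 10 lb, and 0.8% HbA1c with a standard deviation of 1.5%. The values are attributed to prior work.

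After that calculation the section adds: "This trial has been powered for 2 phases of hypothesis testing". Phase 1 compares each intervention arm with control. Phase 2 compares with each other the arms that succeeded in phase 1. On the size of the phase 2 differences it says: "We expect that the magnitude of difference between intervention arms will be less than that of successful intervention arms compared with control". Phase 2 is tested "with a 2-sided alpha of .017 to adjust for up to 3 comparisons".

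The section gives no effect size and no power figure specific to phase 2. It does not say which phase the listed effects belong to.

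**The concern.** Every pair of arms has the same planned size, the two phases use the same alpha, and only one standard deviation is given per outcome. With these fixed, power depends only on the true difference, and a smaller difference has lower power. The section therefore claims power for phase 2 while expecting phase 2 differences to be smaller than those versus control, and it shows no calculation for those smaller differences.

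What is at stake is how the comparison of supportive, competitive and collaborative incentives will be read. Phase 2 is the formal test between them. A reader told that the trial was powered for it could give a non-significant between-arm result more weight than the design supports.

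**Working it through.** **Inputs, all from the Power section.** 90 per arm; 10% dropout, so 90 × 0.9 = 81 evaluable per arm; two-sided alpha .017 in both phases; effects and standard deviations as listed. The standardized effects d are:
- Steps: 1100/2000 = 0.550
- Weight: 6/10 = 0.600
- HbA1c: 0.8/1.5 = 0.533

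**Method.** Two-sample t test with n = 81 per arm and 2 × 81 − 2 = 160 degrees of freedom. The noncentrality is d × √(81/2) = 6.364 × d, and the two-sided critical value at .017 is 2.412. Power is the probability that the noncentral t falls beyond ±2.412.

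**Step 1: reproduce the stated figure.**

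| Outcome | Noncentrality | Power |
|---|---|---|
| Steps | 3.500 | 86.0% |
| Weight | 3.818 | 91.9% |
| HbA1c | 3.394 | 83.6% |

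The normal approximation gives 86.7%, 92.4% and 84.3%. The stated 80% holds for the listed effects.

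**Step 2: smallest difference with 80% power.** Solving for 80% power gives d = 0.512. As a check by the normal approximation, √(2/81) × (2.387 + 0.842) = 0.1571 × 3.229 = 0.507.
- Steps: 0.512 × 2000 = 1024, which is 93% of 1100
- Weight: 0.512 × 10 = 5.1 lb, which is 85% of 6
- HbA1c: 0.512 × 1.5 = 0.77%, which is 96% of 0.8

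The normal approximation gives 1015 steps, 5.07 lb and 0.76%.

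**Step 3: power for smaller differences.** The article does not quantify the phase 2 difference. The fractions below are therefore assumptions that show a range.

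| Between-arm difference as a share of the listed effect | Steps | Weight | HbA1c |
|---|---|---|---|
| 90% | 77% | 85% | 74% |
| 75% | 59% | 67% | 55% |
| 50% | 26% | 31% | 24% |

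The normal approximation agrees within about 1 percentage point (for example 59.4%, 68.3% and 56.3% at 75%).

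**The case against.** The strongest objection is that the article never assigns the listed effects to a phase. If they were meant as between-arm differences, phase 2 has the stated power, phase 1 has more, and nothing conflicts. This cannot be excluded, because the sources of the values are not at hand. It is the less natural reading. The calculation comes before the two phases are introduced. The Background describes the earlier randomized trial as showing that gamification raises physical activity, and the Objective presents the testing of more types of incentive as the new step. It would also be a demanding assumption. At .017 with 81 per arm, an arm needs an observed HbA1c advantage over control of about 2.412 × 1.5 × 0.1571 = 0.57% to enter phase 2. A further 0.8% between arms would put the better arm near 1.4% over control, and the article states no such expectation. If this reading was intended, the section still needs to say so.

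Four further points stand:
- **No figure is wrong.** The stated 80% reproduces, and it is attached to the listed effects, not separately to phase 2.
- **The shortfall is conditional.** A reader might infer that phase 2 simply lacks 80% power. The article does not support that, because the expected reduction is not quantified. Reductions of up to about 7% (steps), 15% (weight) or 4% (HbA1c) keep 80%.
- **Null phase 2 results are not bound to occur.** A reader might infer that they are likely whatever the truth. At 75% of the listed effects, a significant result is still more likely than not for all three outcomes.
- **The net effect of other design features is unknown.** A reader might add that clustering within groups of three lowers power further. The article gives no intracluster correlation, and the planned adjustment for baseline could raise power above that of an unadjusted t test.

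It may also be said that a condensed article can leave the phase 2 detail to a fuller document. That would answer a complaint of omission. The point here is an affirmative statement that the next sentences undercut.

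**Conclusion.** The claim of power for two phases is not supported by the single calculation given. If the listed effects are differences from control, phase 2 has 80% power only for between-arm differences of at least about 1020 steps, 5.1 lb or 0.77% HbA1c. Differences that small relative to the listed effects leave little room for the reduction that the section itself expects.

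This rests on 81 evaluable per arm, an unadjusted two-sample t test, the listed standard deviations applying to between-arm contrasts, and the versus-control reading of the effects. The power figures at fractions of the listed effects are illustrations, since the article gives no phase 2 difference.

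The point is worth correcting but is not critical. The phase 1 power, the alpha and the test sequence are untouched by it. Nothing in the article says that non-significance will be read as equivalence, so that risk lies with later readers and is not an error in the plan.

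**What to change.** Three changes to the Power section and to the reporting of phase 2:

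1. Say that the power of at least 80% applies to the phase 1 comparisons with control. If the listed effects were meant as between-arm differences, say that instead.
2. On the versus-control reading, replace the claim of power for two phases with the phase 2 detectable differences. Suggested wording: With 81 evaluable participants per arm and a two-sided alpha of .017, comparisons between intervention arms have 80% power for differences of about 1020 steps, 5.1 lb or 0.77% HbA1c; power is lower for smaller differences.
3. Report phase 2 contrasts as estimates with confidence intervals, and state that a non-significant contrast will not be read as equivalence.

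The cost is wording and a less favourable stated figure for phase 2. Enrollment is complete at 361, and the change requires no additional patients, data or tests.

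### Phase 2 tests every arm-versus-arm pair at a flat .017, which is valid; a step-down after the first rejection would find more within the same 0.05 per outcome

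*Protocol article*

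**What the plan says.** The Power section of the protocol article describes two phases of testing. First: "In the first phase, we will compare each of the 3 intervention arms with control". Then: "In the second phase, we will compare successful intervention arms with each other". The second phase uses a "conservative Bonferroni adjustment of the type I error rate with a 2-sided alpha of .017 to adjust for up to 3 comparisons". The level does not depend on how many pairs are actually tested, or on whether one of them has already been rejected. The section claims that "the overall family-wise error rate of this 2-phase procedure is controlled at 0.05", because only arms that differ from control go forward. It gives no figure for the expected differences between intervention arms, but says: "We expect that the magnitude of difference between intervention arms will be less than that of successful intervention arms compared with control".

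**The concern.** Three arms give three pairwise equalities, and these are logically linked. If one is false, at most one of the other two can be true, because two true equalities would force the third. A flat .05/3 guards against three simultaneous true nulls even after the data have ruled that state out.

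The cost falls on the ranking of the arms. To name one social incentive as better than both others, two pairs must be rejected. Under the flat rule the second rejection must clear the same bar as the first.

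**Working it through.** **Inputs from the Power section.** A "sample size of 360 participants (90 per arm"), 10% dropout, so 90 × 0.9 = 81 evaluable per arm; HbA1c SD 1.5; two-sided .017, which is .05/3 = .0167 rounded.

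**The plan's own figure.** Power ≈ Φ(δ / (SD·√(2/81)) − z), with z the two-sided .017 critical value:
- steps, 1100 / 2000: 86.7%
- weight, 6 / 10 lb: 92.4%
- HbA1c, 0.8 / 1.5: 84.3%

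The claim that the sample "will provide at least 80% power" is reproduced. It concerns differences of the size planned against control.

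**Proposed rule, per outcome.** If all three arms pass phase 1, test the smallest pairwise p value at .0167. If it is rejected, test each of the other two pairs at .05 (Shaffer step-down). If only two arms pass, their one comparison stays at .0167.

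**Error bound.**
1. Some arm equals control. The step-down acts only when all three arms pass phase 1, and that event already contains a phase 1 error. It adds nothing to the flat rule's family-wise error.
2. All arms differ from control and are equal to each other. A false rejection needs at least one of three pairs with p ≤ .0167: at most 3 × .0167 = .05.
3. All arms differ from control and exactly one pair is equal. A false rejection needs that pair's p ≤ .05: at most .05.
4. All arms differ from control and from each other. No pairwise rejection is false.

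The step-down keeps every flat-rule rejection, so it never finds less.

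**Size of the gain.** Both phases were simulated for one outcome (at least 1,000,000 runs per pattern, shared control, normal test statistics, independent participants). The effects are assumptions, in HbA1c points versus control, because the article gives no arm-versus-arm effect.

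| True effects | Both true differences shown, flat | Step-down |
|---|---|---|
| 0.8 / 0.8 / 1.0 | 0.9% | 2.1% |
| 0.8 / 0.8 / 1.2 | 7.2% | 13.1% |
| 0.8 / 0.8 / 1.4 | 27.2% | 38.5% |
| 1.0 / 1.0 / 1.6 | 36.5% | 51.2% |

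Repeat runs agreed to about 0.1 percentage point.

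**What does not change.** The chance of at least one phase 2 finding is the same under both rules: 0.248 at 0.8/0.8/1.2 and 0.580 at 0.8/0.8/1.4. In the latter pattern all three arms pass phase 1 in about 75% of runs.

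**Realised family-wise error, flat to step-down.**
- 0.8/0.8/1.4: 0.006 to 0.019
- 0.8/1.6/1.6: 0.017 to 0.044
- 1.6/1.6/3.0: 0.017 to 0.050

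The error approaches the bound when effects are large. The guarantee comes from the proof, not from the maximum over a chosen set of patterns.

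**The case against.** The strongest reply is that nothing here is wrong. The plan calls its adjustment conservative, the family-wise claim holds per outcome, and a flat rule is simple, with confidence intervals that agree with its decisions. All of that stands. A reader might infer that the .017 rule is invalid or that the family-wise claim fails; the Power section does not support that reading.

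The second reply is that the gain is small where the plan expects to be. The article expects arm-versus-arm differences to be the smaller ones, and at 0.8/0.8/1.0 a phase 2 decision changes in only 1.7% of trials. At 0.8/0.8/1.4 it changes in 12.6%, but there the best arm has 1.75 times the planned effect. This stands too. It is tempting to say that the step-down rescues phase 2 where power is scarcest. It does not: the first rejection must still clear .0167, and nothing changes unless all three arms have beaten control.

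Third, the gain is not quite without cost. Realised error rises within its bound, and 98.3% intervals stop matching the decisions. That is a fair description, but a small price.

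Finally, an analysis plan that is not shown could refine the procedure. That is possible, but the article does state a rule, and the point concerns that rule.

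**Conclusion.** The flat .017 in phase 2 is valid per outcome and needlessly inefficient. A step-down triggered by a first rejection finds everything the flat rule finds, sometimes more, and keeps the two-phase family-wise error per outcome at or below 0.05.

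The benefit is confined to second and third differences once all three arms have succeeded. In the patterns tabulated it ranges from about 1 percentage point (2.1 − 0.9 = 1.2) to about 15 (51.2 − 36.5 = 14.7), depending on how far the best arm stands apart. These sizes rest on assumed effects, on the plan's n, SD and dropout, and on no correlation within the groups of three. The bound needs only pairwise tests that hold their nominal levels. It is stated for one outcome at a time and says nothing about multiplicity across the three primary outcomes.

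Severity is low: an optional improvement, not a correction.

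**What to change.** State for phase 2, separately for each outcome: if all three intervention arms beat control, the pair with the smallest p value is tested at two-sided .0167; if it is rejected, each of the other two pairs is tested at .05. If only two arms beat control, their single comparison stays at .0167. Report step-down adjusted p values and let them carry the decision.

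The restriction on a lone pair matters. With two equal effective arms and one ineffective arm, phase 1 can already spend .0167 on the ineffective arm. Testing the lone pair at .05 would then take the family-wise error to about 0.066.

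The cost is one sentence and no new data. Confidence intervals at 98.3% can still be shown, with a note that they do not correspond one to one with the step-down decisions. The change should be made before the statisticians, who are blinded under the In-Person Visit and Randomization section, see arm assignments.

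### The 0.05 family-wise error claim holds only within one primary outcome and with a same-outcome gate; across the three primary outcomes the rate is about 0.09 to 0.13

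*Protocol article*

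**What the plan says.** The Outcome Measures section lists three primary outcomes side by side, with no order of priority: "The primary outcomes were change in HbA_1c_, change in weight in pounds, and change in mean daily steps", each measured from baseline to the end of the year.

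The Power section sets out two phases of testing. First: "In the first phase, we will compare each of the 3 intervention arms with control". Then: "In the second phase, we will compare successful intervention arms with each other". The second phase is run "with a 2-sided alpha of .017 to adjust for up to 3 comparisons". The power statement for all three outcomes uses the same two-sided .017. The section closes by saying that "the overall family-wise error rate of this 2-phase procedure is controlled at 0.05", and the only reason it gives is that an arm must differ significantly from control before it is compared with another intervention arm.

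Neither these sections nor Statistical Analysis adjusts across the three outcomes, ranks them, requires success on all three, or says that the 0.05 applies to each outcome separately. The article also does not say on which outcome an arm must have beaten control to count as successful.

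**The concern.** A level of .017 pays for one factor of three. The first phase has two such factors, arms and outcomes, and so nine primary tests. The gate between phases limits which arm-to-arm comparisons are run. It does nothing about having three outcomes on which a first-phase test can come out falsely positive.

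A reader of the results would set a single significant result, out of nine primary tests, against a stated 5% chance of any false claim. If the 5% holds only outcome by outcome, that reader understates the risk. A second, smaller issue is that the gate is not tied to an outcome. If an arm that beat control on steps may then be compared with another arm on HbA1c, the gate argument no longer protects HbA1c.

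**Working it through.** **Inputs from the article.** Three primary outcomes (Outcome Measures). From Power: three arm-versus-control comparisons, up to three arm-to-arm comparisons, two-sided alpha .017 per test, 90 per arm, 10% dropout, and effects (SD) of 1100 steps (2000), 6 lb (10) and 0.8% HbA1c (1.5%). Evaluable per arm: 90 × 0.9 = 81.

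**Input not in the article.** The correlation between the three outcomes. It is assumed equal for each pair and varied from 0 to 0.8.

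**1. The plan's own power figure.** Two-sample t-test, 160 degrees of freedom, noncentrality = (effect/SD) / √(2/81), where √(2/81) = 0.1571. The critical value at .017 is 2.412.

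| Outcome | Effect/SD | Noncentrality | Power at .017 |
|---|---|---|---|
| HbA1c | 0.533 | 3.394 | 83.6% |
| Steps | 0.550 | 3.500 | 86.0% |
| Weight | 0.600 | 3.818 | 91.9% |

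The statement of at least 80% is reproduced.

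**2. Origin of the level.** 0.05/3 = 0.0167, which rounds to .017. It is a split by three only. The rounding is trivial: 3 × 0.017 = 0.051.

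**3. Error rate for one outcome, same-outcome gate.** Bonferroni bound 0.051. Simulation with a shared control (1,000,000 replicates per configuration) gives:

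- no arm effective: 0.045
- all three arms equally effective, so that errors arise only in the second phase: 0.045
- two arms equally effective: 0.034
- one arm effective: 0.032

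The two-phase argument works here.

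**4. Error rate across three outcomes.** First-phase tests: 3 arms × 3 outcomes = 9. Bonferroni bound: 9 × 0.017 = 0.153. If all nine tests were independent: 1 − (1 − 0.017)^9 = 0.143. Simulated with a shared control under the global null:

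| Between-outcome correlation | Rate |
|---|---|
| 0 | 0.130 |
| 0.3 | 0.126 |
| 0.5 | 0.117 |
| 0.7 | 0.103 |
| 0.75 | 0.098 |
| 0.8 | 0.093 |

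If instead all arms are equally effective on every outcome, the false positives come from the second phase and the rate runs from 0.129 (correlation 0) to 0.091 (0.8).

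**5. Cross-outcome gate.** Suppose all three arms truly work on steps, none works on HbA1c, and success on steps admits an arm to second-phase tests on HbA1c. Then all six pairwise HbA1c comparisons among four equal arms can be run at .017. The chance of at least one false positive is the upper tail of the studentized range for four means at 2.387 × √2 (2.387 is the two-sided normal critical value at .017). It is about 0.080, for that one outcome.

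**6. A trial-wide 0.05 by Bonferroni.** 0.05/9 = 0.0056 per test. The simulated rate is then 0.046 (correlation 0) to 0.034 (0.8). With the critical value now 2.811 and the noncentralities of step 1, power with 81 per arm is 71.9% for HbA1c, 75.3% for steps and 84.1% for weight.

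**The case against.** The strongest reply concerns what the sentence is about. It speaks of this two-phase procedure, and the procedure described just before it consists only of arm comparisons. *Overall* may then mean over both phases within one outcome, and on that reading the claim holds (step 3). This stands to the extent that the sentence should not be called flatly false. It does not remove the point: three unranked primary outcomes are powered in the same paragraph, nothing limits the claim to one of them, and a reader can fairly take it as trial-wide. Reading the first-phase .017 as a split over outcomes instead of arms does not help either, since nine tests at .017 remain.

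A second reply is that distinct primary outcomes need no joint adjustment. That is a defensible design choice, but the 0.05 must then be claimed per outcome. A full analysis plan, not shown here, may define the family that way or set a hierarchy. The published sentence would still need its qualifier.

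Three stronger readings are tempting and are not supported:

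- *The true rate is more than double 5%.* This depends on a correlation that the article does not give. It holds up to about 0.7 and fails from about 0.75. Correlations that high among HbA1c, weight and steps would be extreme, but the statement must stay conditional.
- *The plan lets an arm cross from one outcome to another.* The wording permits this but does not state it. Judging success on the same outcome is the more natural reading.
- *The power statement is wrong.* It is correct at the level that the plan uses. The loss at 0.05/9 arises only if a trial-wide claim is chosen.

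**Conclusion.** The claim is stated more broadly than the procedure supports. At .017 with the two-phase gate, family-wise error is held at about 0.05 for a single primary outcome (simulated 0.045, bound 0.051), provided that an arm reaches the second phase only on the outcome on which it beat control. Across the three primary outcomes the rate under the global null is about 0.13 at zero correlation, falling to about 0.09 at 0.8, with a bound of 0.153 whatever the correlation. If the gate were applied across outcomes, the rate for a single outcome could reach about 0.08.

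These figures assume equal arms, a shared control, approximately normal test statistics and the same correlation for each pair of outcomes. The bound needs only that each test holds its own level. The point matters because this is the error-rate statement for the trial's primary tests. It does not affect the sample size, the data or the stated power at .017.

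**What to change.** 1. Restate the claim in the Power section as family-wise error controlled at 0.05 within each primary outcome.
2. Add that across the three primary outcomes the rate is about 0.09 to 0.13 for between-outcome correlations of 0.8 down to 0, with an upper bound of 0.15.
3. State that success is judged per outcome, so that an arm is compared with other intervention arms only on the outcome on which it differed from control.

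These are changes of wording in the protocol and analysis plan, carried through to the results report. They need no further participants or data.

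Only if a trial-wide 5% claim is wanted: run both phases at 0.05/9 = 0.0056 per test and restate power with 81 evaluable per arm as about 72% for HbA1c, 75% for steps and 84% for weight. The cost is that at least 80% power then holds for weight alone.
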